### Statistical analysis

The statistical analysis will be performed with the SPSS 25.0 software. Continuous variables are reported as mean ± standard deviation (SD) or median (interquartile range), while categorical variables are expressed as frequencies or percentages. Parametric data were analyzed using ANOVA or the Kruskal-Wallis H-test, whereas nonparametric comparisons employed chi-square tests (*χ*^2^ tests) or Fisher’s exact probability tests. The primary outcome is the 24-h PONV incidence rate. Superiority testing will assess whether the experimental intervention’s efficacy exceeds that of the control group, derived from literature-derived baseline PONV incidence (control group p₁ = 0.610) and hypothesized 30% relative risk reduction (experimental group p₂ = 0.427). The predefined superiority margin (*δ*) is set as an 18.3% absolute risk reduction (i.e., the incidence in the experimental group must be ≤ the incidence in the control group – δ, where *δ* = 0.183). A single-tailed *Z*-test will be used to compare the incidence difference between the two groups, calculating the risk difference (risk difference, RD) with corresponding 97.5% one-sided confidence interval (equivalent to 95% two-sided CI upper bound). Superiority will be established if the CI upper limit for RD remains below *δ*. Relative risk (RR) with 95% CI will supplement these analyses. Nonparametric alternatives (Fisher’s exact test) will substitute when normal approximation assumptions are violated. Post-hoc exploratory analyses are used to examine heterogeneity in the primary outcome across predefined subgroups, including age <25 years, female sex, history of motion sickness/PONV, smoking status, surgery duration >200 min, and hypotension duration >60 min. Logistic regression is employed to adjust for treatment-covariate interactions of subgroup factors. A *p*-value <0.05 will be considered statistically significant. Except for the superiority test, which employs a one-sided test, all other tests are two-sided.

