For the aforementioned high-risk factors, various antiemetic regimens with multimodal pharmacological interventions targeting distinct pathophysiological pathways are currently incorporated in orthognathic surgery, such as serotonin 3 (5-HT3) receptor antagonists, glucocorticoids, opioid-sparing analgesic protocols, nasogastric decompression, and throat packs. These interventions exhibit distinct pharmacokinetic profiles, therapeutic efficacy, and adverse effect spectra, with no monotherapy demonstrating complete PONV prevention (15). Combination therapy is superior to monotherapy. In current anesthesia practice, dexamethasone combined with palonosetron, a second-generation 5-HT3 receptor antagonist with prolonged receptor-binding kinetics (mean elimination half-life: 40 h), constitutes the baseline dual antiemetic regimen for high-risk patients (16, 17). Acupuncture therapy is also endorsed as one of options for preventing PONV in the Fourth Consensus Guidelines for the Management of PONV in 2020 (3). Commonly used acupoints include the Neiguan point (PC6) on the pericardium meridian, the Zusanli point (ST36) on the stomach meridian, and the Hegu point (LI4) on the large intestine meridian. While the precise mechanism remains incompletely elucidated, it may involve modulating sympathetic nerve activity and gastrointestinal function, promoting potential gastrointestinal motility to prevent PONV.

Acupuncture has been well-documented in literatures on abdominal, gynecological, and otolaryngological surgery in PONV prophylaxis. Nevertheless, its application in orthognathic procedures remains limited. Existing acupuncture protocols predominantly involve intraoperative acupoint stimulation that terminates upon patient transfer from the operating theater. It is unclear whether acupuncture can offer comparable benefits in preventing PONV in orthognathic surgery patients, as it does in other abdominal surgeries. Current evidence derives primarily from trials comparing acupuncture monotherapy against single-agent pharmacotherapy, notably omitting guideline-recommended combination prophylaxis in control arms – a methodological limitation that reduces external validity and impedes clinical implementation (18–20).

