### Intervention

Upon entering the operating room, the acupuncturist generates a randomization sequence via the Random.org website (https://www.random.org/) to access the corresponding sealed envelope containing group allocation details. Before induction of anesthesia, the acupuncturist applies the assigned thumb-tack devices bilaterally according to the randomized allocation. Both groups receive two thumb-tack devices: a real needle (0.25 mm × 2.0 mm, disposable sterile press needles) and a sham needle with identical appearance but no needle tip. In Group A, the real device is bilaterally applied to the PC6 acupoint – located three finger breadths proximal to the wrist crease between the palmaris longus and flexor carpi radialis tendons – while the sham device is bilaterally positioned at the non-acupoint site six finger breadths proximal to the wrist crease and 2 cm ulnarly. Group B receives the inverse configuration, with sham stimulation bilaterally at PC6 and real stimulation bilaterally at the non-acupoint site. The sham site maintains a 3 cm radius free of established acupoints to prevent collateral stimulation (Figure 3). No deliberate De Qi sensation is elicited during application. Opaque sterile patches will be applied to both intervention sites to conceal the allocation information (Figure 4), with devices remaining *in situ* for 24 postoperative hours. All acupuncture-related procedures are performed in strict accordance with aseptic principles to minimize the risk of infection. Both groups receive standardized PONV prophylaxis per guidelines (18): dexamethasone 5 mg, palonosetron 0.075 mg, propofol target-controlled infusion (TCI) 0.5 μg/mL, and pharyngeal packing.

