All patients receive intravenous cefuroxime axetil 1.5 g immediately post-induction, with an equivalent prophylactic dose administered 3 h intraoperatively. Axillary temperature maintenance ≥36 °C is ensured using forced-air warming blankets as required. Flurbiprofen 50 mg is administered intravenously 6–7 min prior to surgical skin incision to prevent inflammatory pain. Local infiltration anesthesia with 4% lidocaine containing 1:100,000 epinephrine is applied to both mandibular and maxillary regions. Pharyngeal packing with sterile gauze is implemented to minimize blood ingestion. Controlled hypotension during Le Fort I osteotomy is maintained at a mean arterial pressure (MAP) 50–65 mmHg through combined administration of sevoflurane, metoprolol, and urapidil. Sufentanil 5 μg combining with palonosetron 0.075 mg are administered 30 min prior to surgical closure as preemptive analgesic and antiemetic therapy. Postoperative analgesia was provided via patient-controlled intravenous analgesia (PCIA) using a solution containing sufentanil 100 μg and flurbiprofen 200 mg, diluted with normal saline to a total volume of 100 mL. The pump was programmed with a basal infusion rate of 2 mL/h, a bolus dose of 2 mL, and a lockout interval of 15 min. Neuromuscular blockade reversal with sugammadex is selectively administered based on the patient’s muscle strength recovery. Rescue therapy for refractory PONV consists of intravenous droperidol 1 mg. Supplemental tramadol 100 mg IV is administered if Numerical Rating Scale (NRS; 0 = no pain, 10 = worst pain imaginable) scores exceed 3 points despite three consecutive effective PCIA boluses, with repeat dosing permitted as clinically indicated.

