### Data collection and outcome assessment

Following informed consent acquisition, research staff will document baseline parameters including gender, age, height, body weight, body mass index (BMI), history of motion sickness, smoking status, ASA classification, and Apfel risk score (6). Perioperative records will encompass surgical duration, intraoperative fluid balance, controlled hypotension period (defined as MAP <65 mmHg), extubation latency (time from surgery completion to tracheal tube removal), and cumulative dosages of anesthetic agents (propofol, sufentanil, remifentanil).

A designated and trained clinical research specialist will conduct follow-up assessments twice daily (08:00–10:00 and 18:00–20:00) during the initial 24 postoperative hours, evaluating PONV severity, pain intensity, and adverse events. The 12-point PONV assessment scale documents the worst nausea episode per evaluation window, in which 0 = no nausea, 10 = most severe nausea, and 11 = retching/vomiting.

The primary outcome measure of this study is the 24-h incidence of any episode of nausea, vomiting (retching or vomiting) or both (i.e., postoperative nausea and vomiting) postoperatively. PONV is defined as the PONV score ≥1.

Secondary outcomes include: (1) stratified PONV incidence at 0–2 h, 2–6 h, and 6–24 h intervals; (2) peak PONV severity scores during these timeframes; (3) 24-h postoperative QOR-15 score to assess the recovery of patients; (4) the total number of patient-controlled analgesia pump pressed by the patient within 24 h; (5) overall NRS pain score within 24 h; (6) postoperative hospital length of stay; (7) the consumption of tramadol and droperidol.

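### Two of the six planned subgroup factors, surgery and hypotension duration, are measured after needle placement without being marked as such, and age enters only as a single cut at 25 years

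*Protocol article*

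**What the plan says.** The Statistical analysis section describes the subgroup work in one sentence that opens "Post-hoc exploratory analyses are used to examine heterogeneity in the primary outcome across predefined subgroups" and then names the factors: "age <25 years, female sex, history of motion sickness/PONV, smoking status, surgery duration >200 min, and hypotension duration >60 min". The model follows: "Logistic regression is employed to adjust for treatment-covariate interactions of subgroup factors". The section closes with "Except for the superiority test, which employs a one-sided test, all other tests are two-sided", so the interaction tests are two-sided at 0.05.

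On timing, the Intervention section states: "Before induction of anesthesia, the acupuncturist applies the assigned thumb-tack devices bilaterally according to the randomized allocation". In Table 1, PC6 stimulation starts in the column before induction, while the durations of surgery and of controlled hypotension sit in the next column, during surgery. The Data collection and outcome assessment section lists them apart from the baseline variables: "Perioperative records will encompass surgical duration, intraoperative fluid balance, controlled hypotension period (defined as MAP <65 mmHg".

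On mechanism, the Background says of acupuncture that "it may involve modulating sympathetic nerve activity and gastrointestinal function". It also counts intraoperative controlled hypotension among the PONV risk factors particular to orthognathic surgery. The Anesthetic management section fixes a pressure range but no duration: "Controlled hypotension during Le Fort I osteotomy is maintained at a mean arterial pressure (MAP) 50–65 mmHg".

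Age is recorded at baseline, with eligibility from 18 to 64 years. In the subgroup list it appears only as the cut below 25.

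**The concern.** A subgroup analysis compares randomised groups within each stratum only if stratum membership could not have been changed by treatment. Age, sex, motion-sickness or PONV history and smoking meet that condition. Surgery duration and hypotension duration do not meet it by design, because they arise after the needles are in place. The plan lists all six together and does not mark the two durations as different in kind.

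Hypotension duration is the more exposed of the two. The article names a mechanism by which acupuncture might influence blood pressure, and it treats hypotension as a predictor of PONV. A variable that treatment may shift and that also predicts the outcome is a poor choice for defining an effect-modifier subgroup. A reader of the final paper could take a PC6 effect seen only in patients with long hypotension as a randomised finding.

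The age point is separate and concerns efficiency. A logistic interaction model accepts age as a continuous term. Reducing it to one cut discards information in tests that already have little power.

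**Working it through.** **1. Order of events.**

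| Factor | When fixed | Source |
|---|---|---|
| Age, sex, motion-sickness history, smoking | Before randomisation | Data collection; Table 1 |
| Needle placement | Before induction, after allocation | Intervention; Table 1 |
| Surgery duration | During surgery | Data collection; Table 1 |
| Hypotension duration | During surgery | Data collection; Table 1 |

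The last two rows follow needle placement.

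**2. The plan's own figure.** With p1 = 0.610, p2 = 0.427, mean 0.5185, Zα = 1.645 and Zβ = 0.84, the printed formula gives

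n = (1.645·√0.49932 + 0.84·√0.48257)² / 0.183² = (1.1624 + 0.5835)² / 0.033489 = 91.02,

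rounded up to 92 per group as stated. This covers the primary comparison only. No power is stated for any interaction.

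**3. Power of a two-level interaction.** On the risk-difference scale, with v = 0.61·0.39 + 0.427·0.573 = 0.4826, n = 108 per arm (216/2) and subgroup share f,

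SE = √[v/(n·f) + v/(n·(1−f))].

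Suppose the subgroup effects differ by the whole planned effect, 0.183:

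- f = 0.5: SE 0.134, power 28%
- f = 0.3: SE 0.146, power 24%
- f = 0.2: SE 0.167, power 20%

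With 92 per arm and f = 0.5, power is 24%.

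**4. Information kept when a continuous covariate is cut** (assumption: linear effect). For a normal covariate the fraction kept is φ(c)²/[f(1−f)], where f is the share above the cut c:

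- 50/50: 0.3989²/0.25 = 0.64
- 30/70: 0.3477²/0.21 = 0.58
- 20/80: 0.2800²/0.16 = 0.49

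For an exponential covariate the fraction is f(ln f)²/(1−f), giving 0.48, 0.62 and 0.65 for the same upper shares. The loss therefore depends on the distribution, which the article does not give.

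Simulated logistic interaction (N = 216, 2,000 runs, normal covariate, two-sided 0.05):

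| Interaction slope (log-odds per SD) | Continuous | Cut 50/50 | Cut 30/70 |
|---|---|---|---|
| 0.5 | 35–38% | 25% | 22% |
| 0.9 | 77% | 58% | 51% |

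**5. Distortion from a post-allocation factor** (every input except the control rate is an assumption). Treatment has no effect on PONV. A shared cause has correlation 0.6 with duration and log-odds 0.8 per SD on PONV. The intercept is ln(0.61/0.39) = 0.447, and the cut is at 0. Treatment shifts duration by a set amount. False risk differences above and below the cut:

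- no shift: 0.000 and 0.001 (zero within simulation error)
- −0.2 SD: +0.013 and +0.012
- −0.5 SD: +0.034 and +0.031

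The sign follows the assumed direction of the shift. The larger values are 0.013/0.183 = 7% and 0.034/0.183 = 19% of the planned effect. The two subgroups are offset by nearly the same amount, so the contrast between them, which is what the interaction tests, moves less. With correlations of 0.5 or 0.6 and cuts at −0.5, 0 and +0.5 SD, the false contrast was at most about 0.005 for the −0.2 SD shift and about 0.011 for −0.5 SD.

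**The case against.** The strongest reply is that measurement after needling does not by itself create bias; the needle must change the duration. For surgery duration the article offers no route. For hypotension, pressure is deliberately lowered with drugs to a target range, by anaesthesiologists whom the Discussion describes as blinded. Both arms receive a real needle, so only an effect specific to PC6 could separate them. The Background is tentative about mechanism. All of this stands and makes a large distortion unlikely. It does not turn the durations into baseline factors: the protocol fixes a pressure range, while the subgroup is defined by time spent below 65 mmHg.

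A reader might go further and infer that the split would produce a false interaction. The calculations do not support that. Under the assumptions tried, both subgroups were offset by similar amounts and the contrast between them barely moved.

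A reader might also infer that age is split into halves and that a third of the sample is effectively lost. The article does not support that either. The cut is a fixed value, the share below 25 is unknown, and the 64% figure needs a normal covariate, a median cut and a linear effect. A true threshold near 25 would lose little.

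Finally, the coding of an exploratory model may be left to an analysis plan that is not shown, and binary entry of age is the natural reading rather than an explicit statement. That tempers the age point. It does not touch the choice of factors, which the article does fix. The interest in hypotension is clinically reasoned, and descriptive reporting can still serve it.

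**Conclusion.** The point holds in a limited form and is minor. Two of the six listed effect modifiers are post-randomisation variables presented beside baseline factors without distinction. Whether treatment effects within those subgroups are biased depends on whether PC6 needling shifts the duration. That is conceivable for hypotension and has no documented pathway for surgery duration. The size cannot be obtained from the article. Under assumed shifts of 0.2 to 0.5 SD it was about 0.013 to 0.03 in risk difference within each subgroup, and about 0.01 or less between subgroups.

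Cutting age is an avoidable loss of information if its effect is roughly linear, and the amount depends on an age distribution that is not given. Modelling age as continuous would not rescue tests that have about 20 to 28% power for an interaction as large as the whole planned effect, but it costs nothing.

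No inference that the primary result is at risk is warranted. These analyses are labelled exploratory, and the primary test and sample size do not depend on them.

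**What to change.** In the Statistical analysis section:

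1. Limit the treatment-by-covariate interaction tests to factors fixed before randomisation: age, sex, motion-sickness or PONV history, and smoking status.
2. State that age enters the logistic interaction model as a continuous term, and keep the cut at 25 years for display only.
3. Report surgery duration and hypotension duration descriptively by arm. If an analysis of PONV by either duration is kept, label it as post-randomisation and not open to causal interpretation as effect modification.

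The cost is a change of wording. Two exploratory subgroups become descriptive. No new data, visits or participants are needed.

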### Ethics and dissemination plan

The study protocol has undergone tripartite scientific review by the Clinical Research Institute of Peking University Shenzhen Hospital. Four independent clinical experts evaluated the trial’s methodological rigor and operational feasibility. Implementation strictly complies with the Declaration of Helsinki and China’s regulatory requirements for clinical investigations, ensuring ethical integrity and participant safety. Prior to the trial commencement, a comprehensive research plan was meticulously prepared and submitted for rigorous review by the ethics review committee. Following formal approval from the Medical Ethics Committee of Peking University Shenzhen Hospital (approval number: 2025124), the trial achieved prospective registration with the ITMCTR (Trial registration number: ITMCTR2025001713), fulfilling international standards for research transparency.

The participants in this study are patients scheduled for elective surgeries at our institution. On the preoperative day, members of the research team visit each patient at the bedside to provide thorough explanations regarding the objectives and methodology of the study. Prior to obtaining written informed consent, investigators verify participants’ comprehensive understanding of study-related benefits and potential risks. All collected data will use de-identified alphanumeric codes in lieu of personally identifiable information to ensure participant confidentiality during analysis and publication.

Participation in this clinical trial is strictly voluntary. All enrolled subjects retain unconditional rights to withdraw at any stage without compromising their standard perioperative care or incurring therapeutic discrimination. Non-participants and withdrawn cases receive identical evidence-based PONV prophylaxis as per institutional protocols during surgical interventions. The investigative team assumes full financial responsibility for managing study-related adverse events, including emergency medical expenses and extended hospitalization costs attributable to trial participation.

Following trial completion, de-identified research outcomes will be disseminated through international peer-reviewed journals to advance evidence-based management of post-orthognathic PONV. All confidentiality-protected participant data (including demographic records and medical histories) will be permanently excluded from dissemination materials in compliance with HIPAA-compliant standards. This protocol strictly adheres to ethical knowledge generation principles, maintaining equilibrium between scientific transparency and individual privacy preservation throughout the knowledge translation process.

## Discussion

In recent years, due to the rising patients’ expectations for improved quality of life and the advancement of Virtual Surgical Planning techniques, which can precisely simulate aesthetic outcomes, an increasing number of patients have actively requested to undergo orthognathic surgery (10). Notwithstanding inspirational advances in the field, PONV persists as a critical determinant of postoperative recovery trajectories and prolonged hospitalization in orthognathic patients. Severe vomiting may threaten the life safety of patients. Notably, patients demonstrate greater tolerance thresholds for postoperative pain compared to PONV-related distress (21, 22). Compared with pain, PONV prophylaxis remains constrained by limited pharmacological options.

Postoperative pain can be effectively relieved by drugs and nerve blocks, but once PONV occurs, the intraoperative prophylactic agents are ineffective as remedial treatment. Notably, dexamethasone’s antiemetic efficacy necessitates early intraoperative administration to exert an anti-inflammatory effect (23), whereas propofol-based total intravenous anesthesia (TIVA) is restricted to the intraoperative phase. The treatment options for PONV are very limited, so prevention is the focus. Effective prevention can significantly improve patients’ perioperative experience.

The precise pathogenesis of PONV remains incompletely elucidated, with current evidence suggesting multifactorial etiology involving distinct neurobiological pathways (24). Monotherapy targeting single neurotransmitter systems demonstrates limited clinical efficacy due to partial pathway blockade. Current consensus guidelines advocate multimodal prophylaxis combining two or more mechanistically distinct antiemetics for high-risk populations, with dexamethasone plus 5-HT3 receptor antagonists constituting the evidence-based cornerstone regimen (3). It is well known that the type of surgery is a crucial risk factor for PONV. Procedures involving laparoscopic surgery, weight loss surgery, gynecological surgery, and cholecystectomy are well-established risk amplifiers. Currently, most clinical studies on PONV revolve around these types of surgeries (25–30). Orthognathic surgery’s classification remains contentious: the 2007 PONV Management Consensus Guidelines designated it high-risk (31), whereas subsequent 2014/2020 updates rescinded this designation (3, 32). However, even with a combined treatment regimen, the incidence of postoperative nausea was as high as 50% in patients with orthognathic surgery, and even higher in patients with bimaxillary surgery (9). Therefore, in patients undergoing bimaxillary surgery, it may be beneficial to add a third adjunctive preventive measure, namely preoperative intradermal acupuncture, to the baseline dual antiemetic regimen of dexamethasone plus palonosetron (8). Acupuncture, transcutaneous electrical nerve stimulation (TENS), or capsaicin stimulation of PC6/ST36 have been clearly demonstrated to prevent PONV, as non-inferior to conventional antiemetics of metoclopramide, cyproheptadine, promethazine, ondansetron, and dexamethasone (33–35). Practical constraints limit intraoperative acupuncture protocols – most studies employ transient perioperative stimulation without sustained postoperative retention. Once patients leave the operating room, all stimuli are withdrawn. However, postoperative facial swelling and swallowing blood in orthognathic surgery patients remain significant risk factors for PONV. This temporal discontinuity raises the clinical question of whether intraoperative-only acupoint stimulation still effectively prevents PONV requires further clinical research to confirm.

The intradermal needle, a thumb-tack shaped medical device, is subcutaneously implanted to deliver sustained acupoint stimulation through localized mechanical activation. This modality provides continuous regulation of meridian function and qi-blood balance through controlled dermal neuromodulation (36, 37). Clinical evidence supports extended indwelling periods (up to 72 h) with minimal discomfort and unrestricted patient mobility, contributing to its widespread adoption in contemporary practice (38–40). The superficial anatomical placement of PC6 allows precise needle insertion using microfilament devices, effectively avoiding trauma to critical neurovascular structures including the median nerve and radial artery in the wrist region.

To optimize blinding integrity, a forearm region devoid of established acupoints within a 3 cm radius is selected as the sham stimulation site. Participants in the sham group receive superficial dermal stimulation mimicking needle insertion trauma using identical sterile devices. Opaque surgical dressings are symmetrically applied to all intervention sites to preserve allocation concealment. This protocol ensures triple blinding: neither participants, anesthesiologists, nor outcome assessors can visually or tactilely discern active versus sham needle placement.

